Word clouds are a tool which enables qualitative data to be displayed; the importance or frequency is assigned by word size or orientation. In the medical literature, word clouds are mainly used to report qualitative patient interview data [15], although further afield they have been used to stimulate creativity [16, 17].

This article describes the generation of word clouds of terms suggested by individuals with DCM, for diagnosis, treatment, long-term management, and other aspects of DCM, so that they can be used in the PSP survey. The article also outlines how word clouds will be nested within AO Spine RECODE-DCM, in order to evaluate their impact on responses in the online survey. This will give insight into their role and value to stimulate a creative research agenda from respondents to surveys about research priorities.

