## Implementation plan for AO Spine RECODE-DCM

AO Spine RECODE-DCM includes several parallel consensus processes, including a research priority setting partnership and the development of a minimum data set. The AO Spine RECODE-DCM survey will be accessed via a single-entry point, with block randomization to one of the two streams (either Priority Setting Partnership or Minimum Data Set) per stakeholder group (spinal surgeon, other healthcare professionals, persons with DCM and their supporters). This methodology was chosen for efficiency to enable a single recruitment phase. Further detail on the overall process is provided in reference [5].

For participants allocated to the PSP, further 1:1 block randomization will occur to two streams, a survey including word clouds and a second stream without word clouds. For those allocated to the word cloud stream, participants will complete the survey as planned initially. However, after survey completion, respondents will be presented with a brief overview of the development method and aims of the word cloud subproject. Participants will then be presented with each word cloud in turn, with the option to submit further research questions. This approach was taken for two principal reasons. Firstly, to ensure the traditional JLA methodology can be conducted contemporaneously, but still partitioned if required, and secondly, to enable any cross over of responses within the word cloud arm to be considered. Participants will be able to move freely within the survey up until the point they reached a final “thank you” page. Consequently, it will be theoretically possible for participants in the word cloud stream to edit their pre-word cloud form having seen the word clouds. This cannot be tracked by the survey platform. However, by retaining an arm who have no access to the word clouds, any such cross over can be evaluated.

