As part of any JLA PSP, the raw suggestions are processed into their individual questions. Then questions deemed “out of scope” are removed, before the remaining questions are collated into common themes, each represented by a summary question. This process is iterative, with a clear audit trail to track where any submission ends up. Consequently, the overall number of questions submitted, alongside the number deemed “in-scope” research questions and the number linked to a summary question appearing in the final research priority list, will be recorded in this evaluation. These numbers will be compared between streams, and for those in the word cloud stream, before and after viewing the word cloud. Metrics will be evaluated overall and per stakeholder group, as well as specifically for each category of question (diagnosis, treatment, long-term management, and other). The impact of the relative size of a word or its relative competition (the number of other words in the cloud) will also be evaluated, by comparing the number of questions generated that match each word and evaluating for a positive correlation. The use of word clouds will be judged meaningful if they prompt a greater breadth of suggestions across the phases of care. Suitable statistical methods will be used for comparisons based on the distribution of the data.

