## Discussion

Primarily driven by individuals with DCM, word clouds were developed for associations with the diagnosis, treatment, long-term phases of care, and an “other” category. These will be nested within AO Spine RECODE-DCM, in order to evaluate their role in supporting the research uncertainty gathering phase of a JLA Research Priority Setting Partnership.

The diagnosis word cloud highlights prominent symptoms and MRI, the gold standard diagnostic tool. The treatment section highlighted the gold standard treatment—surgical decompression. The long-term management section highlighted disability and tiredness. The other category highlighted ignorance of the condition. Amongst several pervasive themes were pain and psychological consequences such as anxiety and depression.

The perspective of PwCM has been limited within DCM research to date, but wider experience from healthcare shows this can bring critical insights [8]. In one of the few previous DCM examples, our evaluation of PwCM recovery priorities identified that pain, alongside upper and lower limb function, was most valued [18]. This contrasts the current outcomes of research studies not including PwCM input and supports the rationale for AO Spine RECODE-DCM, and its establishment of a minimum data set. The broad range of ideas displayed goes beyond current research foci [23] indicating the value of engaging PwCM in research design [8].

We hypothesize that this PwCM perspective could be enhanced within a JLA PSP. While PSP were developed to ensure the voice of patients is incorporated into setting a research agenda, this is only really considered by the group as a whole during the final consensus meeting. Put specifically, professionals do not have the opportunity to reflect on “patient” perspectives until summary questions have already been generated and shortlisted. In this nested methodological study, we will therefore evaluate whether the PwCM generated word clouds can help the group as a whole develop research questions and specifically, priority research questions.

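### The planned question counts do not separate new questions from a respondent's own repeats, and only the word cloud stream has a second pass on which to repeat

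*Protocol article*

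**What the plan says.** All of the relevant text is in the Protocol article, mostly under Implementation plan for AO Spine RECODE-DCM.

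- **Allocation.** "For participants allocated to the PSP, further 1:1 block randomization will occur to two streams". The article describes these as "a survey including word clouds and a second stream without word clouds".
- **Second pass.** Cloud-stream respondents first complete the standard survey. "Participants will then be presented with each word cloud in turn, with the option to submit further research questions". There are four clouds, and the Discussion says that they were built to match the predefined survey sections. No second pass is described for the other stream.
- **Metrics.** The evaluation records "the overall number of questions submitted, alongside the number deemed “in-scope” research questions and the number linked to a summary question appearing in the final". The list meant here is that of the agreed priorities for research.
- **Comparisons.** "These numbers will be compared between streams, and for those in the word cloud stream, before and after viewing the word cloud". The counts are also split by stakeholder group and by question category.
- **Processing.** After out-of-scope items are removed, "the remaining questions are collated into common themes, each represented by a summary question", and an audit trail follows each submission.
- **Criterion.** The clouds are to be judged meaningful if they widen the range of suggestions across the phases of care. No measure of that range is given beyond the counts by category.
- **Aim.** The Introduction says of the evaluation: "This will give insight into their role and value to stimulate a creative research agenda from respondents to surveys about research priorities". The Abstract and the Conclusion leave the value for a more creative agenda to further research.

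**The concern.** All three metrics count questions. A respondent who asks about imaging on the standard form, and asks again when the diagnosis cloud appears, adds to the count twice although the agenda has gained nothing. Only cloud-stream respondents are given a second place to do this. Randomization cannot balance it, because the extra pass belongs to one stream by design.

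Repeats are plausible, though not documented. The clouds return respondents to headings that they have just answered, and some of the largest words are familiar topics: "The diagnosis word cloud highlights prominent symptoms and MRI, the gold standard diagnostic tool", and surgical decompression in the treatment cloud.

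At stake is the main reading of the nested study. The Discussion gives its principal objective as broader gathering of research uncertainties. A count that rises without any new question does not measure that.

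**Working it through.** The article states no sample size, power, significance level or effect size for this comparison, so there is no figure of the plan's to reproduce. The check follows one repeated question through the metrics and then illustrates the possible size.

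**1. One repeat through each metric.** Suppose that a first-form question is in scope and linked to a priority summary question, and that the respondent repeats it after a cloud.

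- Submitted: +1.
- In scope: +1.
- Linked to a priority summary question: +1, because the metric counts the questions linked, not the summary questions reached.
- Distinct summary questions reached by that respondent: +0.

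**2. In symbols.** Let a be the mean number of first-form questions (equal in expectation in the two streams), d the mean number of after-cloud repeats and m the mean number of new after-cloud questions.

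- Counts as planned: (a + d + m) − a = d + m.
- Repeats removed: (a + m) − a = m.
- After-cloud count: d + m. It cannot be negative, and a single repeat makes it positive.

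**3. Ratio with no new ideas (m = 0).** If a share r of first-form questions is repeated, d = r·a and the ratio is (a + r·a)/a = 1 + r. This gives 1.05, 1.10, 1.20 and 1.30 for r = 5%, 10%, 20% and 30%.

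**4. Share of an apparent gain (assumed figures).** Take 4 first-form questions and 1 after-cloud entry per respondent. The apparent gain is 1/4 = 25%. Let s be the share of after-cloud entries that are repeats. The real gain is (4 + 1·(1 − s))/4 − 1:

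- s = 20%: 4.8/4 − 1 = 20%
- s = 50%: 4.5/4 − 1 = 12.5%
- s = 80%: 4.2/4 − 1 = 5%

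Here s is a share of after-cloud entries, whereas r in steps 3 and 5 is a share of first-form questions. The two are not interchangeable.

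**5. Simulation with no new ideas in either stream.** All inputs are assumed: first-form questions negative binomial with mean 4 and dispersion 2, each repeated with probability r, a two-sample t-test at two-sided 0.05, and 4000 runs per setting. The table shows how often the result is significant in favour of the clouds. The nominal rate is 2.5%.

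| n per stream | r = 5% | 10% | 20% | 30% |
|---|---|---|---|---|
| 50 | 5% | 8% | 16% | 30% |
| 100 | 7% | 12% | 30% | 54% |
| 200 | 8% | 20% | 55% | 85% |

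Counting each respondent's repeats once gives 2% to 3% in every cell.

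**6. The breadth criterion.** A repeat under the same heading does not widen coverage across phases. A repeat under a different heading could appear to. The Discussion names pain, anxiety and depression as themes running through several clouds. A pain question entered under treatment and repeated at the long-term cloud would raise the count in a second category.

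**The case against.** The strongest reply has five parts.

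- **No rule says that repeats count twice.** Correct. The conclusion rests on how the metrics are worded and on the absence of any rule for repeats. The full protocol may hold one. A reader might infer that the plan prescribes double counting, and the article does not support that. It does fix the metrics as counts of questions, and followed as written these include repeats.
- **The criterion is breadth, not volume.** This stands in part. A repeated imaging question under diagnosis does not meet the criterion. But breadth has no measure other than the same counts by category, and step 6 of the working shows how a repeat can enter there.
- **Creativity is deferred.** The Abstract and the Conclusion leave the value for a more creative agenda to later work, and the Abstract gives the target as number and relevance of questions. The counts should therefore not be faulted for failing to settle creativity. The point here is narrower: they do not separate new from repeated.
- **Repeating is speculative.** Respondents are invited to add further questions, and nothing in the article shows that they restate old ones. The clouds also feature less familiar topics, such as ignorance of the condition. The rate is unknown, and the figures above are illustrations only.
- **Novelty judged by theme can undercount.** A summary question stands for a theme, so an after-cloud entry within a theme already touched may still be a different question. This stands, and the fix allows for it.

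**Conclusion.** The concern holds in a limited form. The three counts do not distinguish new questions from a respondent's own repeats, and only the cloud stream is described as having a second pass. A higher count there, or a positive after-cloud count, does not by itself show new ideas or greater breadth.

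A reader might go further and infer that the study cannot show whether the clouds stimulate new questions. The documents do not support that. After-cloud entries are collected apart from the standard form, and each submission can be traced to its summary question, so most repeats can be found without new data.

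The size cannot be stated, because neither the repeat rate nor the number of respondents is given. The ratio 1 + r assumes only that no new question arises. The simulated rates rest on the assumed distribution, test and sample sizes as well.

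**What to change.** Keep the planned counts. From the links already recorded, add two measures and base the breadth judgement on them.

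1. **Distinct summary questions per respondent**, overall and by phase of care, compared between streams. Class each after-cloud entry as new to that respondent or as repeating one of their own standard-form entries, looking across all sections. In the split by phase, count a summary question where the respondent first entered it. Report a different question within a theme already touched as its own class. Do not discard it.
2. **Summary questions, and those on the final priority list, supported only by after-cloud entries**, that is, by no standard-form entry from either stream.

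The article concedes that cloud-stream respondents can edit the standard form after seeing the clouds, and that this is not tracked. Such edits can blur the new-or-repeat classification and measure 2. The overall between-stream comparison in measure 1 does not depend on where an entry was typed, so it should carry most weight.

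The cost is a little more analysis work and a possibly smaller reported gain. Removing repeats does not separate the effect of the clouds from that of being asked a second time. That should be stated as a limit on the conclusion.

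### The before/after comparison of question counts within the word cloud stream cannot measure what the clouds add, whichever way 'after' is read

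*Protocol article*

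**What the plan says.** All of this is in the protocol article, under 'Implementation plan for AO Spine RECODE-DCM', unless noted.

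- Allocation: "further 1:1 block randomization will occur to two streams, a survey including word clouds and a second stream without word clouds".
- First pass in the cloud stream: "For those allocated to the word cloud stream, participants will complete the survey as planned initially".
- Second pass, once the survey is complete: "Participants will then be presented with each word cloud in turn, with the option to submit further research questions". No second pass is described for the stream without clouds.
- Outcomes: "the overall number of questions submitted, alongside the number deemed “in-scope” research questions", plus the number that feed into a summary question on the final priority list.
- Comparisons: "These numbers will be compared between streams, and for those in the word cloud stream, before and after viewing the word cloud". The article does not say whether *after* is the add-on alone or the running total.
- Methods: chosen to suit the distribution of the data. No test, significance level, sample size or expected rate is given.
- Success: the clouds count as meaningful if suggestions become broader across the phases of care.
- Editing: "it will be theoretically possible for participants in the word cloud stream to edit their pre-word cloud form having seen the word clouds", which the platform cannot track.

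The Introduction gives the reason for nesting the clouds in the survey: "in order to evaluate their impact on responses in the online survey".

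**The concern.** The study asks whether clouds prompt questions that would not otherwise have been submitted, so a useful contrast should be centred on zero when the clouds do nothing. A count before against a count after would do that if the same task were done twice. Here the first count comes from a full survey and the second from an optional extra page offered to people who have just written down their ideas.

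At stake is how the result is read. On one reading, helpful clouds could be reported as yielding significantly fewer questions. On the other, any trickle of additions could be reported as a gain. No test chosen to suit the distribution cures this, because the fault lies in the two quantities compared.

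**Working it through.** **Inputs.** The article gives no rates or sample size, so there is no stated figure to reproduce. Assumed: first-pass mean m1 = 4 questions per person; second-pass mean m2 from 0.1 to 6; 30 or 100 participants per stream; overdispersed counts (Poisson with a gamma-distributed personal rate, shape 1 or 1.5, shared across both passes); two-sided 5% level. The survey layout is taken from the article.

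**Step 1: what each contrast estimates.** Let B be first-pass and A second-pass questions per person. Write the mean of A as m2 = r + c, where r is what a second request would yield without clouds and c is what the clouds add. The target is c. Ignore edits to the first form for now.

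| Contrast | Expected value | Equals c only if |
|---|---|---|
| (a) further questions only, A − B | r + c − m1 | r = m1 |
| (b) cumulative, (B + A) − B = A | r + c, never negative | r = 0 |
| Between-stream totals | (m1 + r + c) − m1 = r + c | r = 0 |

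**Step 2: reading (a) in numbers.** Take r = 0, so that everything added is due to the clouds.

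- c = 1 (1/4 = 25% more questions): expected difference 1 − 4 = −3.
- c = 2 (2/4 = 50% more): 2 − 4 = −2.
- m2 = 4: 4 − 4 = 0.
- m2 = 6: 6 − 4 = +2.

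Simulated signed-rank tests agree. At m2 = 1 or 2, *after* is significantly lower in 97% to 100% of runs and significantly higher in none. At m2 = 4 the test rejects in about 4% to 6%. At m2 = 6 *after* is significantly higher in 84% to 89% of runs with 30 participants and 100% with 100. The sign follows the relative yield of the two passes.

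**Step 3: reading (b) in numbers.** Each difference equals A, which is zero or positive. A sign test therefore depends only on how many people add anything. Five give p = 2 × 0.5^5 = 0.0625; six give p = 2 × 0.5^6 = 0.031. With a mean of only 0.25 added questions (shape 1.5), the chance that a person adds none is (1.5/1.75)^1.5 = 0.794, so 0.206 add at least one. The binomial probability of six or more is 61% with 30 participants and over 99.9% with 100. With a signed-rank test (shape 1), rejection is 24% (30 participants) and 96% (100) at a mean of 0.1, and 98% to 100% from a mean of 0.5 upward.

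**Step 4: the contrast is blind to the source of A.** Only r + c enters either reading. Clouds that add 1 question per person with r = 0, and useless clouds where being asked again yields 1, produce the same within-stream data and the same test result.

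**Step 5: the randomised comparison.** Between-stream totals also estimate r + c. With no cloud effect (c = 0), Mann-Whitney tests on totals favour the cloud stream in 24% (30 per stream) and 66% (100) of runs at r = 2, and in 54% and 97% at r = 4. First-pass counts alone differ at about the nominal rate (4% to 8%). The total does keep one advantage: cloud-prompted questions typed back into the first form are still counted as extra, whereas within the stream they inflate *before*.

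**The case against.** The strongest reply has four parts.

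1. **No test is promised.** The article says numbers will be compared by suitable methods and names no null hypothesis or p-value. The definition of *after* may sit in an analysis plan that is not shown. This stands in part: a descriptive tally would fit the wording and do little harm. But the objects compared are stated in the article, and neither definition of *after* makes their difference a measure of cloud effect.

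2. **The comparison does not decide the study.** This stands. Success is defined by breadth, a between-stream comparison is planned, and so is a correlation of word size with matching questions. Before and after figures could also be informative as proportions in scope or as a spread over categories; the fault is in comparing raw counts.

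3. **The simulated figures depend on assumed rates.** This stands. The near-certain decrease under reading (a) needs an add-on that yields clearly less than the first survey, and the result reverses at a second-pass mean of 6. Under reading (b) questions really were added, so rejection shows that the null is trivial. It is not a false report of additions.

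4. **The no-cloud arm handles contamination.** The article says that "by retaining an arm who have no access to the word clouds, any such cross over can be evaluated". That concerns edits to the first form. The before/after contrast stays inside one stream, and locking the first form would leave it unchanged.

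A reader might go further and infer that the survey layout fixes the result. The documents do not support that. Only the direction is fixed, and only on the cumulative reading; significance still depends on how many people add something.

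**Conclusion.** The point holds as a fault in a secondary comparison. Reading (a) is shifted down by the whole first-pass yield, so clouds adding 25% to 50% more questions would look like a decrease unless the add-on out-yields the first survey. Reading (b) cannot be negative and cannot separate the clouds from being asked again. The algebra needs only the layout described in the article. The percentages rest on an assumed first-pass mean of 4, overdispersed counts and 30 or 100 participants, and they illustrate the size of the problem without predicting this study's result.

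It would also be wrong to infer that the study's conclusion depends on this contrast, or that the randomised comparison isolates the clouds. The first is contradicted by the breadth criterion. The second fails because only the cloud stream is described as having a second opportunity to answer.

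**What to change.** Replace the before/after comparison of counts with an estimate for the cloud stream:

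- new, non-duplicate in-scope questions submitted on the cloud pages, per participant;
- the share of participants adding at least one such question;
- both overall and by category of question, with 95% confidence intervals and no test against the first-pass count.

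Rest inference on the randomised between-stream comparison, and state that it estimates the effect of the clouds together with the extra opportunity to answer, because no second pass is described for the stream without clouds.

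The cost is a change of analysis wording, with no new data and no change to the survey. What is lost is a within-stream test result that says nothing about the clouds.

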Following the 2-week period, the submitted words and their respective votes were reviewed by the AO Spine RECODE-DCM Management Group [ODM, ES, DK, IS, BMD, OH] and duplicated words were removed. By mutual agreement, words considered to be out of scope were removed, and words felt to be better reflected in a different section were moved. Through consultation with representatives of the other Healthcare Professional stakeholder group (ES, SS) and discussion amongst the management group, some additional word suggestions were put forward. The aim of this was to include the perspective of an additionally under-represented stakeholder group [23] (other healthcare professionals) while ensuring this remained patient-centered by presenting any suggestions back to the group.

The final lists were then re-posted to the group as a series of polls, to allow members to review the list and vote for the words with which they most agreed [Supporting Information 2]. Users could continue to submit additional suggestions, which were then available to be polled. Users could not vote more than once. This second-round exercise ran for a further 2 weeks. The findings were processed by the management group, to combine duplicates and remove out of scope suggestions. Word clouds were generated using WordArt.com (California, USA) for each major section. The size of the word was proportional to the number of votes it received. Words without a vote were not included. The first iteration of the output was used, without modification.

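### A positive correlation between word size and matching questions cannot by itself show an effect of size, because size is the patients' vote count; the no-cloud stream should be the benchmark

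*Protocol article*

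**What the plan says.** The Methods section of the protocol article fixes how the clouds were drawn: "The size of the word was proportional to the number of votes it received". The votes came from members of the online support group, who were polled "to allow members to review the list and vote for the words with which they most agreed".

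The Implementation plan then states a word-level analysis. "The impact of the relative size of a word or its relative competition (the number of other words in the cloud) will also be evaluated", and this is to be done "by comparing the number of questions generated that match each word and evaluating for a positive correlation". No background frequency is named for it, and the text does not say whether pre-cloud questions, post-cloud questions or both are counted.

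The same section provides for a randomized control: "a survey including word clouds and a second stream without word clouds". It also says of the question counts (all submitted, in scope, and linked to the final priority list): "These numbers will be compared between streams, and for those in the word cloud stream, before and after viewing the word cloud". That sentence comes before the word-level analysis and refers to those three counts.

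**The concern.** Size was never varied independently of topic. A large word is one that many patients agreed with, so it differs from a small word both in display and in how widely the concern is shared. The stated analysis looks at the sum of the two influences and calls it the impact of size.

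The link between votes and unprompted questions is plausible for at least part of the sample. Persons with DCM and their supporters, the population from which the voters came, form one of the responding stakeholder groups. Some prominent words, such as MRI and surgery, are also topics that professionals could raise without a prompt.

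At stake is the reading of the result. A positive correlation could be reported as evidence that larger words prompt more questions when it shows only that popular topics are popular.

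**Working it through.** The article gives no expected correlation, question number, significance level or power for this analysis, so there is no figure of its own to reproduce. The check asks how the raw correlation behaves when clouds have no effect.

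**Inputs from the article**
- Words: 87 re-polled + 39 added = 126 (Abstract), before second-round merging and removals.
- Votes: every word polled at least once, maximum 47 (Results).
- Four clouds: 126 / 4 = 31.5, so about 31 words each if analysed cloud by cloud.

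**Assumptions, not in the article**
- Votes log-normal (log-scale mean 1.8, SD 1.0), limited to 1–47.
- Unprompted question rate per word = votes^b × exp(N(0, 0.7)), scaled to 100 or 300 matching questions per stream (a quarter of that per cloud).
- Poisson counts with identical rates in both streams, so the cloud does nothing.
- Test: one-sided 5% Spearman correlation of votes with the cloud-stream count.

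To gauge b, compare a 47-vote word with a 1-vote word. The ratio of expected questions is 47^0 = 1, 47^0.25 = 2.6 and 47^0.5 = 6.9.

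**Share of runs with a significant positive correlation, no cloud effect**

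| b | 126 words pooled | about 31 words per cloud |
|---|---|---|
| 0 | about 5% | about 5% |
| 0.25 | 58–78% | 20–36% |
| 0.5 | 97–100% | 54–74% |

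The ranges run from 100 to 300 questions, and repeat runs agree within a few percentage points. When votes are correlated instead with the word-level difference between cloud and no-cloud streams, the positive rate is 4–7%.

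**Second model.** Here votes and natural question frequency have a latent correlation rho, and a positive result means r > 0 with two-sided p < 0.05 (nominal 2.5%).

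| rho | 126 words | 30 words |
|---|---|---|
| 0 | 2–3% | 2–4% |
| 0.2 | 26–39% | 14–15% |
| 0.4 | 73–91% | 38–46% |
| 0.6 | 98–100% | 77–88% |

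At rho = 0.4 with 126 words and 300 questions, the mean correlation is 0.29 in the cloud stream and 0.29 in the stream that saw no cloud. The raw statistic therefore cannot tell the two explanations apart. Benchmarked on the no-cloud stream, the false-positive rate is 1.4–3.1% across all settings.

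The benchmarked analysis keeps useful power. With a true size effect (rate multiplied by votes^0.3, 126 words, 300 questions) it is significant in 71% of runs at rho = 0.4 and 83% at rho = 0.

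**The case against.** The strongest reply is that the bias depends on a link the article never quantifies. At b = 0 or rho = 0 the raw correlation behaves as it should. The study's own rationale suggests a weak link for professionals, whose questions are thought not to align well with patients' concerns. Timing may weaken it further: "Participants will then be presented with each word cloud in turn, with the option to submit further research questions", so popular topics may already have been used up in the standard survey. This stands. A reader might infer that the analysis is bound to come out positive, and the article does not support that.

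A second reply is that the article is condensed and leaves the test to suitable methods chosen by the distribution of the data, so the benchmark may be specified elsewhere. It is fair to say that the text is silent on using the no-cloud stream here, not that it rules it out. But the article does fix the measure, a correlation, and its reading, an impact of size. A test chosen by distribution does not remove confounding.

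A third reply is that little hangs on this analysis. It is an addition with no decision rule, and the article's stated criterion for a meaningful result is greater breadth of suggestions across the phases of care. That also stands and limits the weight of the point.

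**Conclusion.** The point holds in a limited form. As described, a positive correlation would not establish that word size prompts questions, because size and topic popularity are the same variable. How often it would mislead depends on three unknowns: the strength of the vote–question link, the number of matching questions, and whether the clouds are pooled. Over the non-zero links of b = 0.25 to 0.5, false-positive rates run from 20% to 100% against a nominal 5%; with no link there is no bias.

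A reader might also infer that the trial's main comparison is compromised. It is not: the between-stream comparison of question totals rests on randomization and does not use word size.

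**What to change.** Code the questions from both streams to the same word list, preferably without the coder knowing the stream. Count all matches per word over the whole survey, taking pre- and post-cloud answers together in the cloud stream. Fit a count model with word, cloud category, stream and stream × log(votes), and take the interaction as the size effect. Because size was never separated from votes, describe it as a shift of questions towards larger words.

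Report post-cloud-only counts descriptively. The no-cloud stream has no post-cloud box, so testing them against its full survey would compare unlike things. In one check (100 post-cloud against 300 control questions, no size effect), already-used topics were assumed to halve the post-cloud popularity slope. That comparison was falsely negative in 26%, 67% and 99% of runs at b = 0.25, 0.5 and 1. A post-cloud restriction would also miss cloud-prompted edits to the earlier form, of which the article says "This cannot be tracked by the survey platform".

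State in the plan that the raw correlation alone will not be read as an effect of size. The cost is a change of analysis wording, a little extra coding of the no-cloud stream's questions, and an estimate that carries the sampling noise of two counts and so may be less precise than the raw correlation. The survey itself need not change.
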